## Background

Cardiovascular disease (CVD) is a leading cause of death and disability globally. Dyslipidemia is a major modifiable risk factor for the development of atherosclerotic plaques [1]. Systemic inflammation also plays a central role in the atherosclerotic process from initiation through progression and rupture of plaques [2, 3]. Observational studies suggest that the risk of acute myocardial infarction (AMI) in persons with hyperlipidemia is three times that of the population with normal lipid status. A reduction in serum cholesterol is strongly associated with a reduction in CVD risk [4, 5]. Secondary prevention after AMI has improved in recent decades, but readmissions and death following AMI remain important challenges. Although new lipid-lowering medications are effective in reducing low-density lipoprotein (LDL) cholesterol levels, clinical guidelines advocate addition of non-statin agents [6], but their cost/efficacy is debatable even in high-risk patients [7].

From a public health perspective, lifestyle modification, including dietary changes, is considered a first step in controlling and treating CVD risk factors [8]. However, patients at highest risk of premature death, AMI, and re-hospitalization are those with known CVD [9]. Consequently, international guidelines recommend secondary prevention strategies to reduce subsequent cardiovascular risk, such as evidence-based pharmacological therapy and adherence to diet and physical activity regimens [10]. Studies have shown positive effects on cardiovascular risk factors of a Nordic diet, in which berries and oats are important elements [11, 12]. However, food supplement clinical trials that include subjects with overt disease are scarce, and there is a need for well-planned and well-executed controlled intervention studies of sufficient size and duration to provide a firm evidence base for dietary guidance in both healthy individuals and those suffering from heart disease [13–15].

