### Study population and patient selection

Subjects in this multicenter study will be recruited from among patients referred to Sahlgrenska University Hospital Gothenburg, Umeå University Hospital, Lund University Hospital, Västerås general hospital, Karlstad general hospital, and Örebro University Hospital for coronary angiography/PCI due to ST-segment elevation myocardial infarction (STEMI) or non-ST-segment elevation myocardial infarction (NSTEMI). STEMI is defined as chest pain suggestive of myocardial ischemia for at least 30 min prior to hospital admission with time from onset of symptoms less than 24 h, an ECG with new ST-segment elevation in two or more contiguous leads of ≥ 0.2 mV in leads V2–V3 and/or ≥ 0.1 mV in other leads, or a probable new-onset left bundle branch block. NSTEMI is defined as a combination of onset of symptoms such as central chest pain or aggravated angina pectoris, with or without ECG changes, with ST-segment depression or an inverted T-wave and rise and/or fall of troponin-T or troponin-I above the established margin of an AMI. Study inclusion and exclusion criteria are defined in Table 2.

**Table 2 Tab2:** Inclusion and exclusion criteria

Inclusion criteria • STEMI or NSTEMI • Completed coronary angiography/PCI • Male and female subjects ≥ 18 years • Allocated to atorvastatin at a daily dose of 80 mg • Written informed consent Exclusion criteria • Emergency coronary artery bypass grafting • < 18 years of age • LDL cholesterol < 2.0 mmol/L • Daily intake or the intent to initiate daily intake of bilberry in any form or daily intake of > 15 g of oatmeal or equivalent • Previous randomization in the BIOAMI trial • Inability to provide informed consent	

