### Sample size calculation, data management, and statistical analysis

To the best of our knowledge, no previous intervention study of bilberry/oats with LDL cholesterol as an endpoint in AMI patients has been conducted. Required sample size is calculated on the basis of bilberry-specific interventions from four smaller randomized studies in at-risk populations [18], from our pilot study [27], and from the IMPROVE-IT trial [44], which found a clinically relevant LDL cholesterol-lowering effect of − 0.4 mmol/L when adding treatment with a non-statin agent to standard statin lipid-lowering therapy after AMI. We calculated that 189 subjects would be needed in each study arm to provide 90% statistical power to detect a 0.4 mmol/L or greater reduction in LDL cholesterol in the bilberry or the oat treatment group compared to the reference, with a standard deviation of 1.1 mmol/L and a Bonferroni corrected overall 5% two-sided significance (Statistical Solutions Ltd, Cork, Ireland). The correction is due to two primary hypotheses, (1) bilberry group vs. reference and (2) oat group vs. reference. The same number of participants will be enrolled in the combined bilberry and oat treatment group, for a total of 756 patients in the study. In order to allow for an anticipated dropout rate of ~ 15%, we plan to include 900 patients, 225 in each study arm.

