Data will be transferred in coded form from the participating centers to Örebro University Hospital, where data management and statistical analyses will be performed. All patients will be assigned an identifying number, recorded in the eCRF together with collected data. A code list connected to patient study numbers with individual Swedish resident personal identification numbers will be kept separately, and secured at the participating clinical centers. At completion of collection, a database with data from the eCRF and national registers will be established. The results will be analyzed according to the intention-to-treat principle; that is, subjects randomized to a given group will be followed and assessed without regard to the diet intervention eventually received. A subject can withdraw from the study at any time, if it is the wish of the subject, or if it is medically indicated, as judged by the investigator. Data collected up to the end of follow-up will be used in the final analysis of the study. If a subject wants to discontinue the study participation, data collected until that time point will be analyzed in the study. For the primary outcome, on the original scale or log scale, as appropriate, linear regression with pre-intervention to post-intervention change as outcome, adjusted for the baseline values, will be conducted. In cases of missing outcome data, multiple imputation (MI) will be used. Ordinal variables will be assessed with a *χ*^2^ test for trend or the Mann-Whitney *U* test, and Pearson’s *χ*^2^ test or Fisher’s exact test, as appropriate, will be used to evaluate differences among proportions.

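### The primary LDL model names baseline LDL as its only covariate; adding statin use at admission would gain precision at almost no cost

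*Protocol article*

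**What the plan says.** In the protocol article, the section on sample size, data management and statistical analysis fixes the primary model, a linear regression that takes "change as outcome, adjusted for the baseline values". The baseline value is the only covariate it names. The Randomization section stratifies by study centre and by nothing else.

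Table 2 lists as an inclusion criterion "Allocated to atorvastatin at a daily dose of 80 mg", and the Randomization section repeats that every randomized patient gets this background treatment. The only lipid criterion is exclusion below 2.0 mmol/L. Statin use before admission is neither required nor excluded, and it is not mentioned as a stratification factor or covariate.

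The sample size targets a difference of 0.4 mmol/L for each single-ingredient arm against the reference arm, with 90% power and 189 patients per arm; the 5% level is split between these two comparisons. The spread is given only as "with a standard deviation of 1.1 mmol/L". The article does not say whether this is the SD of LDL change or an SD after baseline adjustment.

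**The concern.** The outcome is LDL change over the same three months in which atorvastatin 80 mg takes effect. A patient who arrives untreated has the whole statin effect still to come; a patient already on a statin has part of it behind them. Two such patients can have the same baseline LDL and quite different expected falls. Baseline LDL alone cannot separate them, so that difference stays in the residual of the primary test and widens the interval for each diet contrast.

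What is at stake is sensitivity to effects below the planned 0.4 mmol/L. The Background cites an LDL reduction of 5–8% for oats, and oats versus reference is one of the two primary hypotheses. For 8% to equal 0.4 mmol/L, LDL would have to be 0.4/0.08 = 5.0 mmol/L; for 5%, 0.4/0.05 = 8.0 mmol/L. At an assumed LDL of 2.0–3.5 mmol/L, 5–8% is 0.10–0.28 mmol/L. In that range the residual SD largely decides whether a real effect is detected.

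**Working it through.** **1. The plan's own figure.** Inputs from the sample size section: difference 0.4, SD 1.1, two comparisons, so two-sided α = 0.025 each, and power 90%.

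n per arm = 2 × [(2.241 + 1.282) × 1.1 / 0.4]² = 187.7, so 188 by the normal approximation. The noncentral t calculation gives exactly 189. The stated 189 reproduces, and power at 189 is 90.2% (normal approximation). This figure takes no credit for a covariate beyond whatever the SD of 1.1 already contains.

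**2. Gain if the SD of 1.1 is the right residual SD.** Let R² be the share of that variance explained by statin use at admission (an assumption). The SD becomes 1.1 × √(1 − R²). For a difference of 0.4:

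| R² | SD | n per arm for 90% | power at 189 |
|---|---|---|---|
| 0 | 1.10 | 188 | 90.2% |
| 0.10 | 1.04 | 169 | 93.1% |
| 0.20 | 0.98 | 151 | 95.6% |
| 0.30 | 0.92 | 132 | 97.6% |
| 0.40 | 0.85 | 113 | 99.0% |

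**3. A plausible size for R².** The documents give no share of previous statin users and no fall by statin history, so this step rests on a simulation with assumed inputs (400,000 patients per scenario):

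- Baseline LDL is N(3.6, 0.9) in naive and N(2.7, 0.6) in treated patients, with values below 2.0 mmol/L removed as in Table 2.
- The mean proportional fall is 50% (SD 15 points) in naive and 0–30% (SD 18 points) in treated patients.
- 10–40% of patients are already treated.

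Each scenario was fitted with baseline LDL alone and then with statin use added. The reduction in residual variance is 1 − (SD with statin use / SD baseline only)².

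| Already treated | Fall in treated | SD, baseline only | SD, with statin use | Variance removed |
|---|---|---|---|---|
| 10% | 30% | 0.58 | 0.56 | 7–8% |
| 20% | 25% | 0.62 | 0.56 | 18% |
| 30% | 15% | 0.695 | 0.559 | 35% |
| 40% | 0% | 0.85 | 0.57 | 55% |

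A second set of assumptions (15–35% treated; falls of 45–50% in naive and 10–30% in treated patients; other baseline means) gave 8–40%. A statin-by-baseline interaction removed at most about 3 further percentage points.

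**4. Power at a smaller effect, middle case (30% treated, 15% fall).** With 189 per arm, SE = SD × √(2/189).

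- Baseline only: SE = 0.695 × 0.1029 = 0.0715. For 0.2 mmol/L, 0.2/0.0715 − 2.241 = 0.56, so power is about 71%.
- With statin use: SE = 0.559 × 0.1029 = 0.0575. Then 0.2/0.0575 − 2.241 = 1.24, so power is about 89%.

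**5. Power at the planned effect.** For 0.4 mmol/L, the largest simulated baseline-only SD (0.85) still gives about 99%, and the middle case gives more than 99.9%.

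**The case against.** The strongest objection is that nothing planned is endangered. At SD 1.1 the trial has its 90% power for 0.4 mmol/L without the covariate. In every simulated scenario the baseline-only SD is below 1.1, so power at 0.4 is about 99% or higher. The protocol does not power for 0.2 mmol/L. This stands: the point is an efficiency gain, not a shortfall against the plan.

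It is also fair that the size depends on assumptions. The 55% end needs no average fall at all in already treated patients, and with few treated patients the gain is small. Other covariates could be listed in a full protocol or analysis plan that is not shown. Still, the article does state the primary model and names one covariate in it, so a suggestion to extend that model is in order; to say that statin history is ignored would go too far.

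A reader might infer that leaving out statin history biases the result or hides a diet effect. It does not: omitting a pre-randomization covariate from a linear model in a randomized trial leaves the contrast unbiased and only widens its interval.

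A reader might also extend the point to lipid-lowering drugs added during follow-up. The Background says that "clinical guidelines advocate addition of non-statin agents", and the sample size section takes its −0.4 mmol/L from a trial result "when adding treatment with a non-statin agent to standard statin lipid-lowering therapy after AMI". If such drugs were started more often in the reference arm, the contrast would shrink: with 20% versus 10% use, 0.4 − 0.4 × (0.20 − 0.10) = 0.36, and power at SD 1.1 is 82.6%. But nothing in the document indicates differential use. The Background sentence goes on to question the value of these agents, the trial schedules LDL only at baseline and week 12, and retaining such values fits the intention-to-treat analysis. How these drugs are recorded and analysed is also detail that a fuller document may hold. This extension is not supported as a finding.

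**Conclusion.** The point holds as a cheap improvement to the primary model. Statin use at admission is a pre-randomization factor, is likely to predict LDL change beyond baseline LDL, and is absent from the one model the article specifies. Under the assumed shares and falls above, it would remove roughly 8–55% of the residual variance. In the middle case that raises power at 0.2 mmol/L from about 71% to 89%. The direction is well founded, but the size is not established, because the documents supply neither the share of previous users nor their expected fall. There is no bias, and power for 0.4 mmol/L does not fall below the planned 90%.

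**What to change.** Record statin use at admission (yes/no) in the eCRF and add it, beside baseline LDL, as a prespecified covariate in the primary regression. Include it in the multiple imputation model as well, so that imputation and analysis agree. An interaction with baseline LDL is optional, since it adds little.

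Do not enter lipid-lowering drugs started after randomization as covariates: they can depend on LDL and hence on the assigned drink, and adjusting for them could introduce bias. As an optional addition, tabulate such drugs by arm and run one supplementary analysis in which LDL values after an add-on are set to missing and imputed with the method already planned. The intention-to-treat analysis stays primary.

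The cost is one eCRF field (assumed to be routinely known at admission) and one model term. The article places the start of enrolment in the future, so the field can be in place from the first patient. Sample size and randomization need no change.

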Primary endpoint • LDL-C cholesterol Major secondary endpoint • Symptom-limited bicycle ergometer test (Watts and estimated VO_2_max) Other secondary endpoints • Dynamic unilateral heel-lift and unilateral shoulder-flexion tests (*n*) • Self-reported activity level (levels 1–6, days/week) • Fasting lipid levels (TC, HDL-C, TGA, small dense LDL-C, apo A, apo B, Lp(a), oxidized LDL) • Fasting insulin, c-peptide, creatinine, glucose, cystatin C • HbA1c, hs-CRP, NT-proBNP, troponin-I, IL-6 • Resting heart rate and blood pressure • Left ventricular systolic function • Untargeted plasma metabolome • Gut microbiota composition	

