#### Exercise capacity

For safety reasons, baseline recordings of exercise capacity and muscle endurance will not be performed following the acute event, and absolute values of change in exercise capacity after intervention can therefore not be estimated. The following assessments are being used in standard clinical care for all AMI patients in Sweden and will be conducted at the 3-month follow-up.

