#### Physical activity scales

The Frändin/Grimby activity scale and the Haskell physical activity scale will be used to subjectively measure physical activity level at baseline and follow-up [41, 42].

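### The tests named for ordinal outcomes leave out the baseline activity score the trial collects: a minor loss of efficiency on one lower-tier secondary endpoint

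*Protocol article*

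**What the plan says.** The Protocol article, under Sample size calculation, data management, and statistical analysis, sets out methods by type of outcome. The primary outcome gets "linear regression with pre-intervention to post-intervention change as outcome, adjusted for the baseline values". For ordinal outcomes: "Ordinal variables will be assessed with a *χ*^2^ test for trend or the Mann-Whitney *U* test". Proportions get a Pearson or Fisher test. No method is named for continuous secondary endpoints.

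Table 1 lists among the other secondary endpoints "Self-reported activity level (levels 1–6, days/week"). The section on Physical activity scales says that two activity questionnaires "will be used to subjectively measure physical activity level at baseline and follow-up". The Randomization section says that allocation is blocked 1:1:1:1 and stratified by study center.

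**The concern.** The article never labels activity level as ordinal, but a score on levels 1–6 falls naturally under the ordinal rule, and it is the only clearly ordinal endpoint in Table 1. That rule names two tests that compare arms without a covariate. In their usual form they cannot take the baseline score, nor the center by which randomization is stratified. The sponsor accepts baseline adjustment for LDL cholesterol in the same paragraph, so leaving it out here looks like a by-product of sorting methods by variable type.

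At stake is precision. Habitual activity differs between people. If a patient's baseline level predicts the 3-month level, an analysis that ignores it leaves explainable variation in the comparison. It also leaves chance imbalance in baseline activity uncorrected.

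**Working it through.** **The plan's own figure.** The only powered endpoint is LDL cholesterol: difference 0.4 mmol/L, SD 1.1, 90% power, 5% two-sided split over two hypotheses (0.025 each).

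- Normal approximation: n = 2 × (2.2414 + 1.2816)² × 1.1² / 0.4² = 2 × 12.41 × 7.5625 = 187.7, so 188 per arm.
- Noncentral t: 189 per arm (power 0.9000), as stated.

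The figure reproduces, and this point does not touch it. The article gives no sample size or power for activity level.

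**Evaluable patients.** 225 enrolled per arm with about 15% dropout: 225 × 0.85 = 191.25, taken as 191.

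**Assumptions.** The article gives no correlation between baseline and 3-month activity and no effect size. The check assumes:

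- a six-level score cut from a normal latent variable;
- a latent treatment shift of 0.3 SD;
- a latent correlation r of 0.3, 0.5 or 0.7;
- two-sided alpha of 0.05 without multiplicity correction;
- 3,000 simulated trials for each r.

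**Simulated power.**

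| r | Mann-Whitney, 3-month score | Mann-Whitney, change score | Rank ANCOVA with baseline | Gain over first column |
|---|---|---|---|---|
| 0.3 | 0.800 | 0.626 | 0.828 | 0.028 |
| 0.5 | 0.801 | 0.766 | 0.874 | 0.073 |
| 0.7 | 0.784 | 0.931 | 0.959 | 0.175 |

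The first column should not depend on r. Its spread from 0.784 to 0.801 is simulation noise: the Monte Carlo standard error is about √(0.8 × 0.2 / 3000) = 0.007. The gains therefore carry an uncertainty of about a percentage point.

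**Low correlation.** The simulation did not go below r = 0.3. As a guide, adjusting a continuous outcome for one covariate multiplies its variance by 1 − r². At r = 0.1 this is 0.99, and √0.99 = 0.995, so the confidence interval is 0.5% narrower, which is negligible.

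**Limits of the check.** It used rank ANCOVA, did not fit a proportional-odds model and did not include center. It covers the six-level score, not the days-per-week measure.

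**The case against.** The tests are valid. Randomization protects the comparison, and a Mann-Whitney test of the 3-month scores makes no proportional-odds assumption. Activity level is one of many other secondary endpoints, and choosing an adjusted model for it is close to preference. All of this stands, and it is why the point is minor.

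Mann-Whitney could also be run on change scores, and the article does not say which score is tested. So it would be too strong to say that the baseline is necessarily thrown away. But change scores are not stated either, and in the simulation they do worse than ignoring baseline at r = 0.3 (0.63 against 0.80) and somewhat worse at r = 0.5 (0.77 against 0.80). Adjustment was better than both at all three correlations.

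A reader might go further and infer that the major secondary endpoint, exercise capacity, also loses precision, because "baseline recordings of exercise capacity and muscle endurance will not be performed following the acute event" and no adjustment is mentioned. The documents do not support this. Watts and estimated VO2max are continuous, so the ordinal rule does not govern them. The regression sentence opens with "For the primary outcome, on the original scale or log scale, as appropriate" and says nothing about other continuous endpoints. The article therefore neither prescribes an unadjusted comparison nor excludes an adjusted one, and a condensed article may leave that to the full protocol or SAP, which are not shown. The Discussion discloses the missing baseline test and points to the baseline activity questionnaires in response, though it does not say that they enter a model. Any percentage gain for Watts would rest on an explained variance that appears nowhere in the article. Listing both Watts and estimated VO2max is a separate matter of specification, and no wrong result follows from it here.

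**Conclusion.** The point holds for the activity scales only. The article names, for ordinal variables, tests that do not take a baseline covariate, although it collects the baseline of its one clearly ordinal endpoint.

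The cost is about 3, 7 and 17 percentage points of power at assumed correlations of 0.3, 0.5 and 0.7, and next to nothing if the correlation is very low. These figures rest on the assumed 0.3 SD shift, about 191 evaluable patients per arm and the six-level latent model. The true correlation is unknown from the article.

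This is a minor efficiency gain on an other secondary endpoint. It raises no question of bias and does not affect the primary analysis or its sample size. No loss of precision on exercise capacity is shown.

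**What to change.** Replace the ordinal rule, for endpoints measured at baseline, with wording such as: the 3-month activity scales will be analysed by proportional-odds regression on treatment, baseline level and study center, each active arm being compared with reference; a Mann-Whitney test of the 3-month scores will be reported as a sensitivity analysis. Rank ANCOVA with the same covariates is an acceptable alternative. State how patients with a missing baseline questionnaire are handled.

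The cost is a change of wording in the protocol or SAP before unblinding. Baseline activity and center are already recorded, so no visit, measurement or patient is added. The downside is the proportional-odds assumption, which should be examined; the Mann-Whitney sensitivity analysis covers its failure.

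Optionally, the SAP could also name baseline activity and center as covariates for 3-month Watts, which would give analytic effect to the mitigation offered in the Discussion. For baseline activity alone, √(1 − r²) gives a confidence interval 4.6% narrower at an assumed r of 0.3 and 13.4% narrower at 0.5. This is a suggestion, not the correction of an error.
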